## Abstract

**Background:**

We report on the design and implementation of a study protocol entitled *Acupuncture randomised trial for post anaesthetic recovery and postoperative pain - a pilot study* (*ACUARP*) designed to investigate the effectiveness of acupuncture therapy performed in the perioperative period on post anaesthetic recovery and postoperative pain.

**Methods/Design:**

The study is designed as a randomised controlled pilot trial with three arms and partial double blinding. We will compare (a) press needle acupuncture, (b) no treatment and (c) press plaster acupressure in a standardised anaesthetic setting. Seventy-five patients scheduled for laparoscopic surgery to the uterus or ovaries will be allocated randomly to one of the three trial arms. The total observation period will begin one day before surgery and end on the second postoperative day. Twelve press needles and press plasters are to be administered preoperatively at seven acupuncture points. The primary outcome measure will be time from extubation to ‘ready for discharge’ from the post anaesthesia care unit (in minutes). The ‘ready for discharge’ end point will be assessed using three different scores: the Aldrete score, the Post Anaesthetic Discharge Scoring System and an In-House score. Secondary outcome measures will comprise pre-, intra- and postoperative variables (which are anxiety, pain, nausea and vomiting, concomitant medication).

**Discussion:**

The results of this study will provide information on whether acupuncture may improve patient post anaesthetic recovery. Comparing acupuncture with acupressure will provide insight into potential therapeutic differences between invasive and non-invasive acupuncture techniques.

**Trial registration:**

NCT01816386 (First received: 28 October 2012)

## Background

Perioperative care has improved over the last decades. To continue this trend it is important note that the quality and speed of post anaesthetic recovery is influenced by multiple factors such as the occurrence of pain, postoperative nausea and vomiting (PONV), paralytic ileus, fatigue and sleep disturbances [1]. Hence, a multimodal approach to prevent and minimise these factors is considered to be essential in order to enhance recovery [2]. These include a series of elements such as providing the patient with thorough preoperative information and education concerning perioperative care, the use of safe and short-acting anaesthetics and optimal dynamic pain relief with minimal use of opioids, management of PONV, enteral nutrition, early mobilization and use of minimal invasive surgery. As a result of optimised anaesthetic protocols, patients might be fully awake earlier and breathe comfortably in the operating theatre [3]. As a result of a more rapid recovery, fewer patients arrive in the post anaesthesia care unit (PACU) sedated, and the period during which they are at risk for airway obstruction and hemodynamic instability is reduced [4].

For achieving an optimised management of postoperative pain and PONV, acupuncture may be a hitherto underestimated option. Interest in the use of acupuncture in anaesthesia leads back to 1971, when James Reston, a *The New York Times* columnist, introduced the western world to the ancient Chinese therapy of acupuncture [5]. Reston underwent an emergency appendectomy in China, and described acupuncture’s success in relieving his postoperative pain. From this point on, several scientists started investigating possible effects of acupuncture. Soon, Bruce Pomeranz revealed that an analgesic effect of acupuncture is mediated by the release of endorphins and can therefore be abolished by the administration of naloxone in humans [6]. Mice deficient in opiate receptors did not experience acupuncture-mediated analgesia [7], which confirms the opioid-related mechanism of acupuncture-analgesia. Soon, first articles reported on the benefits of acupuncture anaesthesia in various operative procedures in China [8,9]. As a consequence, first attempts were made to implement acupuncture in the anaesthetic framework [10], for example, as an option for sedation of the patient during tonsillectomy [11]. A new modified method of anaesthesia in open heart surgery combining acupuncture analgesia and controlled respiration was established at the Department of Anaesthesiology in Gießen, Germany [12]. Since then, general anaesthesia has markedly improved and acupuncture anaesthesia cannot be considered a first-line procedure.

However, there is evidence that acupuncture is effective in facilitating multimodal approaches in perioperative care. An approved acupuncture effect is the reduction of PONV and antiemetic consumption by stimulation of the acupuncture point PC 6 [13]. Recent reviews support the effectiveness of acupuncture regimen in reducing postoperative pain, cumulative opioid consumption or opioid related side effects [14,15]. However, trials are of varying quality and show heterogeneity with regard to the applied acupuncture treatments (acupuncture points used, time point of application). Accordingly, a meta-analysis on the effects of acupuncture on the intraoperative analgesic consumption and quality of anaesthesia revealed inconclusive results [16].

We aim to investigate the effects of a three-day permanent needle acupuncture treatment, starting in the preoperative phase at seven different acupuncture points only - five of them bilaterally - on a comprehensive set of above mentioned variables important to anaesthetic recovery (which are, preoperative anxiety, improving anaesthetic protocols, awakening, nausea and vomiting, and postoperative pain).

## Patients and methods

### Study design

The study is a single-center, partially double blinded, randomised pilot trial comparing (a) press needle acupuncture versus (b) no treatment versus (c) press plaster acupressure in a standard anaesthetic setting of programmed gynaecologic laparoscopic operations. Main outcome measure is the time from extubation to ‘ready for discharge’ from the PACU. Analysis of all records is performed by blinded evaluators. The total follow-up period per patient is two days (see Figure 1). The study has been approved by the Ethics Committee of the University of Munich, Germany (reference 009-12) and is in agreement with the Declaration of Helsinki (Version Fortaleza 2012). Trial registration is NCT01816386.

**Figure 1 F1:**
[figure not shown]
**Study design.** Patients are randomly allocated to either the group ACU (press needle acupuncture), no treatment group (control) or the group APU (press plaster acupressure). After surgery, press needles and press plasters will be kept on the patients’ skin for the next two postoperative days or until discharge from the hospital. The listed outcome measures will be assessed at the marked time points respectively.

### Patients

For inclusion, patients must meet the following criteria:

• Age 18+

• Females scheduled for laparoscopic surgery of uterus, adnexa or ovaries

• American Society of Anaesthesiologists (ASA)-score ≤ 2

• Ability to follow study instructions and likely to attend and complete all required visits

• Written informed consent

Subjects presenting with any of the following exclusion criteria may not be included in the trial:

General exclusion criteria:

• Subject without legal capacity

• Subject who is unable to understand the nature, scope, significance and consequences of this clinical trial

• Simultaneously participation in another clinical trial or participation in any clinical trial involving administration of acupuncture within 30 days prior to inclusion

• Subjects with a physical or psychiatric condition which at the investigator’s discretion may put the subject at risk, may confound the trial results, or may interfere with the subject’s participation in this clinical trial

• Known or persistent abuse of medication, drugs or alcohol

• Current or planned pregnancy or nursing women

• Females of childbearing potential, who are not using and not willing to use medically reliable methods of contraception for the entire study duration (such as oral, injectable, or implantable contraceptives, or intrauterine contraceptive devices) unless they are surgically sterilised/hysterectomised or there are any other criteria considered sufficiently reliable by the investigator in individual cases.

Indication specific exclusion criteria:

• Surgery within the last three months

• Chronic pain > three months

• Continuous analgesic medication with opioids longer than three days

• Massive degenerative diseases

• Pre-treatment with acupuncture or trigger point injection within the last two months

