### Randomised treatment allocation, blinding and sample-size estimation

Informed consent will be obtained from each participant. Subjects eligible for participation will be randomly assigned to one of the following study groups by using the Internet based randomisation software RANDOULETTE® (Institute of Medical Information Sciences, Biometry and Epidemiology, University of Munich):

• press needle acupuncture: 25 subjects

• no treatment control: 25 subjects

• press plaster acupressure: 25 subjects

Stratification for age will be performed, and an equal distribution between treatment arms (ratio of 1:1:1) will be warranted.

In this trial we will use acupressure (group C) as an intervention to compare acupuncture (group A). Patients and examiners will be blinded for the patients’ assignment to treatment arms A and C. Therefore, we use press needles (0.2 mm × 1.5 mm; Seirin New Pyonex®, Seirin Corp., Shizuoka City, Japan) in group A and non-invasive Seirin press plasters in group C - a device that has successfully been validated for blinding in acupuncture trials [17]. Press plasters do not contain a needle but a blunt knob and are in all other aspects identical to the press needles. According to group allocation, press needles or press plasters will be administered by an independent acupuncturist at the same defined acupuncture points. Instructions regarding point stimulation for subjects and study staff will also be identical. Thereby, patients and examiners will be blinded as laid down in the trial of Myazaki and colleagues who showed that neither patients nor therapists nor examiners know if a sharp tip or a blunt knob is located below the plaster. In contrast to Myazaki, patients will be allowed to stimulate their press device, so that an additional acupressure effect may be elicited, thereby enhancing the overall effects.

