### Data analysis

The aim of the statistical analysis is the comparison of the main outcome measure (period from extubation to ‘ready for discharge’ from PACU) between the three study groups (intervention groups acupuncture and acupressure and no treatment control). For this variable, an non-normal distribution is assumed. Hence, a nonparametric method, the Kruskal-Wallis test will be applied. *Post hoc* tests will be performed by pairwise comparisons of the three study groups by the Mann-Whitney *U*-test and subsequent Bonferroni adjustment for multiple comparison (*P*-value times three). Primary outcome is defined as the time to discharge from PACU in the press needle acupuncture group in comparison to the no treatment group.

For the secondary target variables, a method according to the distribution of data will be performed. For metric variables, the structure of a normal distribution will be tested by the Kolmogorov-Smirnov test. In case of a normal distribution, a one-way ANOVA will be calculated. Otherwise a nonparametric test for independent observations like the Kruskal-Wallis test will be carried out.

The analysis of categorical data is conducted by the chi-square goodness-of-fit test. The binary case is treated by the chi-square-test of independence.

Data analysis will be performed with the SPSS statistical software system, version 15.0 (SPSS Inc., Chicago, IL, USA) and with SAS/STAT® Software (SAS Institute Inc., Cary, NC, USA). All data entry will be carried out twice.

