## Discussion

The AcuARP trial investigates the effectiveness of acupuncture on post anaesthetic recovery and its use as an adjunct therapy to improve patient’s recovery in the whole perioperative setting.

Inclusion and exclusion criteria were held pragmatic in order to facilitate screening and recruitment. The chosen trial population is homogeneous and the operations undertaken are common; hence a maximised and improved routine care would be of general interest.

Limitations include the restricted sample size as the trial was planned as a pilot study. In case of a positive study outcome, further confirmatory studies will be needed. In addition, a standardised clinical procurement, using strictly standardised anaesthesia and standardised acupuncture regimen may impede generalizability of the findings.

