### Anaesthetic regimen

The choice of a strictly standardised anaesthetic regimen allows for comparability of all intra- and postoperative measures. The decision to conduct the study within the gynaecologic theatre was on the one hand due to the above mentioned uniform study population, on the other hand driven by the fact that the anaesthetic regimen in this clinic is extended for the use of TCI. TCI systems for dosage of propofol have been available since 1997, were initially developed for adult patients, with the dosage based on the basis of simulated concentration of the drug in the plasma for review: [35]. In the following, taking into account the rate at which the drug enters the biophase of other tissues, that is the brain, the systems were adjusted to the concentration in the so-called effector sites. Today, the systems give the possibility to programme the dosage of various intravenous drugs according to different pharmacokinetic models, which, in brief, differ on the basis of research conducted to assess the suggested rates of infusion. The two systems mainly used are the pharmacokinetic models for propofol as established by Marsh [36] and Schnider [37]. The Marsh model operates with fixed rate constants, whereas compartment volumes and clearances are weight proportional. The Schnider model was developed during combined pharmacokinetic-pharmacodynamic modelling studies, adjusting according to total weight, lean body mass, and height. It is recommended for the use in effect-site targeting mode for review: [38].

The time course of plasma/effect-site equilibration is used to describe the rate of removal of drug from the effect-site out of the body. With effect-site targeting, the TCI system manipulates the plasma concentration to achieve the effect-site concentration as rapidly as possible. When the effect-site target concentration is increased, the TCI system briefly increases the plasma concentration to an optimal level above the target effect-site concentration before temporarily stopping the infusion to allow the plasma concentration to decrease to the level of the target effect-site concentration. If the target effect-site concentration is reduced, the system stops the infusion allowing the plasma concentrations to fall, thereby generating a concentration gradient out of the effect-site, until the estimated effect-site concentration has fallen to the new target [38].

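### The primary rank comparison uses neither the planned operation nor the age stratum; adjusting for both is a cheap, optional gain in precision

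*Protocol article*

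**What the plan says.** All places are in the Protocol article.

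- **Patients.** The surgical criterion is "Females scheduled for laparoscopic surgery of uterus, adnexa or ovaries". Procedure, extent and duration are not limited. The other main restriction, "American Society of Anaesthesiologists (ASA)-score ≤ 2", concerns the patient, not the operation.
- **Randomised treatment allocation, blinding and sample-size estimation.** "Stratification for age will be performed, and an equal distribution between treatment arms (ratio of 1:1:1) will be warranted", with 25 patients per arm. No other stratification factor is named.
- **Outcome measures and Table 2.** The endpoint is reached only when the last of three recovery scores is satisfied. Between them the scores rate surgical bleeding, pain, nausea and vomiting, mobility, oral intake and voiding.
- **Data analysis.** Kruskal-Wallis is followed by pairwise Mann-Whitney tests, with P-values multiplied by three. The named contrast is: "Primary outcome is defined as the time to discharge from PACU in the press needle acupuncture group in comparison to the no treatment group". No stratum or covariate is mentioned.
- **Discussion and Anaesthetic regimen.** "The chosen trial population is homogeneous and the operations undertaken are common", and later a reference to the "above mentioned uniform study population".
- **Trial status.** 50 patients had been included at first submission.

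**The concern.** A short adnexal laparoscopy and removal of the uterus are equally eligible. The endpoint is set by the slowest item to recover, and several items plausibly depend on what was done to the pelvic organs. The planned operation is known before randomisation, because eligibility rests on it, yet neither the allocation nor the analysis uses it. Age is used in the allocation and then left out of the analysis.

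Two things are at stake. Variation between operations stays in the error term of the main contrast. And in a single trial with 25 per arm, a visible difference in case mix would leave readers unsure how much of the observed difference, or of its absence, reflects the surgery.

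**Working it through.** **1. The plan's own figure.** Table 3 uses f = 0.4, alpha 0.05, power 0.80 and three groups. Noncentrality is f²N = 0.16 × 66 = 10.56 and critical F(2, 63) is 3.1428, which gives power 0.818. N = 63 gives 0.798, so 66 is the smallest total divisible by three. Adding 15% gives 66 × 1.15 = 75.9, against the plan's 75. The figure reproduces and contains no allowance for procedure.

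**2. A treatment effect to work with.** If two arms share a mean and the third differs by D, then f = D√2/3 and D = 0.4/0.471 = 0.85 SD. If one arm lies midway, f = D/√6 and D = 0.98 SD. The checks below use 0.8 SD, close to the lower of these.

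**3. Chance imbalance.** Take two independent binomials with n = 25. P(difference of at least 5 patients, i.e. 5/25 = 20 points) is 16% at a 30% share of uterine surgery and 20% at a 50% share. The share is an assumption; the article gives no case mix.

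**4. Precision.** Let p be the share of uterine surgery and g the shift it causes, in SDs within a procedure class. The unadjusted variance is 1 + g²p(1−p). A 5-patient imbalance shifts the contrast by 0.20 × g. The last column gives the simulated power change (van Elteren minus Mann-Whitney) for a 0.8 SD effect with 25 per arm.

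| g (assumed) | Variance factor, p = 0.3 / 0.5 | Shift from a 5-patient imbalance | Change in power |
|---|---|---|---|
| 0 | 1.00 / 1.00 | 0 | about −2 points |
| 0.5 | 1.05 / 1.06 | 0.10 SD | about 0 to +1 |
| 0.8 | 1.13 / 1.16 | 0.16 SD | about +3 to +5 |
| 1.2 | 1.30 / 1.36 | 0.24 SD | about +10 to +14 |

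At g = 0.8 and p = 0.5, an arm of 25 carries the information of 25/1.16 = 21.6 patients. A further set of 8,000 simulated trials per scenario, at two-sided 0.05, gave power of 74.2% against 75.7% (g = 0.5), 70.9% against 75.5% (0.8) and 64.0% against 75.5% (1.2). The picture is the same, slightly higher for the weak effect.

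**5. At the plan's multiplicity level.** Bonferroni by three gives 0.05/3 = 0.0167 per pair. Compared with a linear model adjusted for procedure, unadjusted Mann-Whitney power is 57% against 62–63% (g = 0.5) and 48–49% against 62–63% (g = 1). About 2.5 points of each gap come from using a linear model on normal data: with g = 0 the two methods already differ by 62.7 − 60.2 = 2.5 points (p = 0.3) and 61.9 − 59.2 = 2.7 points (p = 0.5). The loss from ignoring procedure therefore persists at 0.0167, but is smaller than the raw gaps suggest.

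**6. False positives.** Over all randomisations, the unadjusted test rejects a true null in about 5% of trials (4.4% to 5.0% across simulations at nominal 0.05). Among trials with an imbalance of at least 5 patients and g = 0.8, the rate is about 7.5% at 0.05 (runs ranged from 7.4% to 8.9%) and about 3% at 0.0167.

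**7. Interpretability.** With g = 1, a true 0.8 SD effect and testing at 0.05, power is 35–39% when the imbalance runs against acupuncture and 90–91% when it runs in its favour. With g = 0.5 the figures are 59% and 85–87%.

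**The case against.** **A reader might infer that a chance imbalance can create an effect.** The documents do not support this as a flaw of the test. Chance imbalance is already part of a randomised test's error rate, which stays at about 5%. The higher rate applies only within the subset of imbalanced trials and needs a fairly strong procedure effect. At the plan's Bonferroni level it is about 3% for g = 0.8, below 5% even there.

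**A reader might also infer that calling the population homogeneous contradicts the eligibility rule.** It does not. The phrase is a relative description: women only, ASA 2 or lower, planned gynaecological laparoscopy at one centre under standardised anaesthesia. Nothing there claims a single procedure or equal surgical extent. Rewording it would be editorial.

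**The benefit rests on undocumented inputs.** This stands. The article gives neither the case mix nor the effect of procedure on recovery time. A uterine versus adnexal split may not track surgical extent, since either class can hold minor and major operations. With a weak effect the gain is negligible.

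**Covariate adjustment belongs in an analysis plan that is not shown.** This stands in part. That plan may already adjust, and its absence here is no fault. But the article itself fixes the stratification factor and the primary tests, so a better choice can be suggested for what it states.

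**It is a pilot.** True, and the Discussion says confirmatory work would follow a positive result. The trial nonetheless has a power target of 0.80 and names one primary contrast.

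**Conclusion.** The stated primary analysis is valid, and nothing on this point is wrong in the sense of bias or inflated error. It leaves unused two pieces of baseline information, planned procedure and the age stratum, that could sharpen the main contrast.

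The size depends on assumptions: two procedure classes, a 30% to 50% share of uterine surgery, normal outcomes, 25 evaluable patients per arm and a 0.8 SD treatment effect. On these, stratifying by procedure is worth anything from a loss of about 2 points of power (no procedure effect) to a gain of 10 to 14 points (1.2 SD). The calculations cover procedure only; the article gives nothing from which to size the effect of adjusting for age. The second benefit is interpretive: a pre-specified adjusted comparison answers the question about case mix that a 16% to 20% chance of a 5-patient imbalance could raise. This is a cheap improvement and optional.

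**What to change.** Before unblinding:

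1. Record a planned-procedure class for every patient from the surgical schedule as it stood before randomisation, for example uterine surgery versus adnexal or ovarian surgery only. Someone blind to allocation and outcome should code it, including for the patients already enrolled. If clinical staff think another grouping tracks extent better, fix that grouping at this point.
2. Pre-specify the acupuncture versus no-treatment comparison as a rank ANCOVA adjusted for planned procedure class and age, or as a van Elteren test stratified on procedure class, at the multiplicity level the plan sets. Report the unadjusted Mann-Whitney test as a sensitivity analysis.
3. Do not adjust for incision-to-closure time. It is measured after randomisation and can differ from what was planned.
4. Tabulate planned procedure class by arm.

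The cost is one coded field and a change of analysis wording. No patients or procedures are added and the running allocation is untouched, which matters with 50 patients already included. The downsides are the loss of about 2 points of power if procedure does not predict recovery, and sparse strata if age and procedure are fully crossed, which rank ANCOVA avoids.
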